#### Procedure for the Intervention Group

The defect will be completely isolated and hemostatized. To enable quick flap closure following the graft material implantation, the flap will be presutured without tying the knot. With minimal pressure, NovaBone Putty and AmnioGuard will be inserted into the test site’s osseous defect until the flap is raised, filling it up to the osseous wall’s highest coronal level. To ensure primary flap closure, the flap will be coronally adjusted and sutured so that the flap edge is positioned 1 to 2 mm coronal to the cement-enamel junction.

#### Procedure for the Control Group

Except for packing osseous defects at control sites with NovaBone Putty and covering the bone graft with A-PRF membrane, the surgical procedure for the control group will be the same as the procedure for the intervention group.

### Statistical Analysis

A calculation of means and SDs will be conducted, and the mean data will be analyzed using a standard statistical method to determine statistical significance. Unpaired and paired 2-tailed *t* tests will be used to evaluate data at baseline and 6 months for each group. A *P* value greater than .05 will be considered not statistically significant, whereas a *P* value of less than .05 will be deemed significant. The results will be calculated using the SPSS software (version 17; IBM Corp). Group A and group B will be compared based on clinical outcomes of plaque index, full-mouth bleeding score, PPD reduction, and CAL gain using an unpaired *t* test.

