**Results:**

Recruitment began on September 16, 2025, and is ongoing. As of manuscript submission, 4 participants have been enrolled. Results are expected to be published in 2027. All the clinical measurements will be recorded after 6 months. It can be anticipated that AmnioGuard membrane with NovaBone Putty will provide additional benefits in the management of chronic periodontitis by promoting better healing and clinical outcomes.

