
### Objectives

This study aims to evaluate and compare the effectiveness of AmnioGuard and A-PRF in combination with NovaBone Putty in terms of gain in clinical attachment level (CAL), reduction in PPD, and radiographic bone fill in infrabony defects before surgery and 6 months after surgery.

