### Sample Size Estimations

The following calculations were performed to estimate sample size:

Mean PPD for AmnioGuard and NovaBone Putty (μ₁) before: 8.6 (SD 1.17) mmMean PPD for AmnioGuard and NovaBone Putty (μ₂) after: 6.9 (SD 1.10) mmThe standard normal deviate (*Z* value) corresponding to a 2-sided significance level (α) of .05, which equals a 95% confidence level, is given by (1–α/2)=1.96Z_(1–β [β=.05; power=95%]) = 1.64 (Z_(1 − β) represents the standard normal deviate corresponding to the study power. With β set at 0.05 (power=95%), the Z value used was 1.64. This differs from Z_(1 − α/2), which corresponds to the significance level (α = 0.05) used in the sample size calculation).Combining the 2 aforementioned equations yields the following: n≥[(Z_[1 – α/2] + Z_[1 – β])^2^ × (σ₁^2^ + σ₂^2^/r)]/(μ₁ – μ₂)^2^Replacing the aforementioned values into the equation yields the following: n≥[(1.96 + 1.64)^2^ × (1.17^2^ + 1.10^2^/1)]/(8.6 – 6.9)^2^=12

Hence, group 1 and group 2 require a minimum sample size of 12. The minimum total sample size required is 24 [13].

All data will be tested for normality using the Shapiro-Wilk test and for homogeneity of variance using the Levene test to ensure that the assumptions for parametric tests are met.

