### Evaluation Outcomes

The primary outcome of this study is radiographic bone fill at 6 months after surgery. This outcome is crucial as it indicates the extent of bone regeneration achieved through the different treatment modalities being tested. The secondary outcomes are PPD reduction, plaque index, papillary bleeding index, and CAL gain.

PPD reduction, which is used to evaluate the decrease in the depth of periodontal pockets, a sign of improved periodontal health, will be measured using an acrylic stent and a UNC-15 probe. Once the acrylic stent is in place, the UNC-15 probe will be positioned at the appropriate angle to access the deepest part of the interproximal pocket within the crevicular space. The point at which the probe makes contact with the stent will be marked in pencil. This will provide a consistent point of reference for subsequent measurements.

Plaque index will be calculated using the Turesky-Gilmore-Glickman modification of the Quigley-Hein index.

Papillary bleeding index will be calculated using the Muhlemann-Son Sulcus Bleeding Index.

CAL gain, which measures the improvement in the attachment of the periodontal tissue to the tooth, indicating successful regeneration, will be measured using a UNC-15 probe positioned at the base of the pocket.

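### Paired before-after tests in each arm cannot show that either membrane adds anything, because both arms share the flap surgery and the putty; they should be descriptive

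*Protocol article*

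**What the plan says.** The Statistical Analysis section of the protocol article plans two kinds of test. The first sentence on testing reads "Unpaired and paired 2-tailed *t* tests will be used to evaluate data at baseline and 6 months for each group", with P below .05 called significant. A later sentence plans an unpaired t test of group A against group B on plaque index, full-mouth bleeding score, reduction in probing pocket depth (PPD) and gain in clinical attachment level (CAL). That between-group list does not name radiographic bone fill, which Evaluation Outcomes makes the primary outcome.

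On treatment, group A receives NovaBone Putty with AmnioGuard, and group B receives NovaBone Putty with an A-PRF membrane. Apart from how the defect is packed and covered, "the surgical procedure for the control group will be the same as the procedure for the intervention group". No arm receives putty without a membrane.

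Four other places bear on how a within-arm change may be read:

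- Objectives sets out to "evaluate and compare the effectiveness of AmnioGuard and A-PRF in combination with NovaBone Putty", from before surgery to 6 months after it.
- Sample Size Estimations uses the before and after PPD means of one treatment, AmnioGuard plus putty.
- Evaluation Outcomes describes "CAL gain, which measures the improvement in the attachment of the periodontal tissue to the tooth, indicating successful regeneration".
- The abstract's Results anticipates that "AmnioGuard membrane with NovaBone Putty will provide additional benefits in the management of chronic periodontitis".

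The main Results section expects no large difference between the groups, although it expects AmnioGuard plus putty to do better.

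**The concern.** A paired test compares a site with itself before surgery. Everything done to the site in between contributes to the change: flap access and debridement, the putty, the flap closure and the membrane. Because the first three are common to both arms and no arm omits the membrane, the paired test cannot separate the membrane's contribution from the rest.

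The practical risk lies in the report. If the groups turn out similar, as the article expects, a natural summary is that both arms improved significantly and did not differ. Readers could take that as two effective membranes. The same summary could readily arise if neither membrane contributed anything. The article fixes the per-arm significance label and contains no statement that guards against this reading.

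**Working it through.** **Inputs.** All are from Sample Size Estimations unless noted.

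- PPD before, AmnioGuard plus putty: 8.6 mm, SD 1.17.
- PPD after, same treatment: 6.9 mm, SD 1.10. The change is 8.6 − 6.9 = 1.7 mm.
- "2-sided significance level (α) of .05".
- "With β set at 0.05 (power=95%), the Z value used was 1.64".
- 12 per group.
- Assumed, because the article does not give them: the before-after correlation r, taken as 0, 0.3 and 0.5; and the part of the change produced by the procedures common to both arms, taken as 1.7, 0.85 and 0.5 mm.

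**Step 1: the article's own figure.** n = (1.96 + 1.64)² × (1.17² + 1.10²) / 1.7² = 12.96 × 2.5789 / 2.89 = 11.56, rounded up to 12. This agrees with the statement "Hence, group 1 and group 2 require a minimum sample size of 12". Both means in the formula belong to the same treatment, so the figure rests on a before-after change and not on a difference between arms.

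**Step 2: SD of the within-patient change.** SD = √(1.17² + 1.10² − 2r × 1.17 × 1.10).

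- r = 0: √2.5789 = 1.606 mm
- r = 0.3: √1.8067 = 1.344 mm
- r = 0.5: √1.2919 = 1.137 mm

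**Step 3: chance that a paired test is significant when the membrane adds nothing.** The test is two-sided at 0.05 with n = 12 and 11 degrees of freedom. The noncentrality is (shared change) × √12 / SD. For a shared change of 1.7 mm this is 5.889 / 1.606 = 3.67 at r = 0 and 5.889 / 1.137 = 5.18 at r = 0.5. The noncentral t distribution then gives, for one arm:

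| Shared change | r = 0 | r = 0.3 | r = 0.5 |
|---|---|---|---|
| 1.7 mm | 91.5% | 97.8% | 99.7% |
| 0.85 mm | 38.8% | 51.5% | 65.6% |
| 0.5 mm | 16.7% | 21.8% | 28.6% |

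The arms are independent, so the chance for both is the square: 84% to 99% at 1.7 mm and 15% to 43% at 0.85 mm, for r from 0 to 0.5.

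**Step 4: the A versus B test in the same situation.** In 20,000 simulated trials per setting, with equal membranes, shared changes of 0.85 and 1.7 mm and r of 0, 0.5 and 0.7, the unpaired test of change was significant in 4.9% to 5.4%. A shared change cancels in the between-arm difference, so this test holds its level.

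**The case against.** The case on the other side has real force.

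- **A reader might infer that the paired tests are planned as proof that a membrane works.** The article does not say so. Statistical Analysis says only that the tests evaluate data in each group, and the regeneration wording in Evaluation Outcomes explains why the outcomes are measured; it is not a decision rule. This stands: the misreading is invited, not stated.
- **The valid comparison is already planned.** The unpaired A versus B test is in the plan, and the closing Conclusions section words its expectation relative to A-PRF plus putty. This also stands. What remains open is that the between-group list omits the primary outcome.
- **The percentages are power, not error rates.** For its own null hypothesis, no change in the site, the paired test holds its 5% level. The figures matter only if the result is reread as a statement about the membrane.
- **A reader might infer that the paired tests would be significant whatever the membranes do.** That is too strong. It needs the shared procedures to give most of the 1.7 mm, and the article does not say what share they give. At 0.5 mm, significance is unlikely. The figures also concern PPD, a secondary outcome; the article gives no bone fill data from which to compute.
- **Scaling and regression to the mean are weak explanations here.** Baseline is before surgery and may follow the initial scaling, so scaling may add little to the tested change. The 5 mm entry threshold lies (8.6 − 5) / 1.17 = 3.1 SD below the assumed mean, which does not suggest heavy selection. Neither is relied on.
- **A head-to-head trial without a putty-only arm is a legitimate design.** Agreed. It does limit what may be concluded, and that is the point.

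None of this gives the per-arm P values a meaning for the membranes.

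**Conclusion.** The point holds as one about inference and wording. The plan fixes per-arm before-after significance tests in a design where they can speak only to the whole package. With the article's PPD figures, 12 per arm and r between 0 and 0.5, an arm whose membrane adds nothing yields a significant paired test with probability 92% to 99.7%, 39% to 66%, or 17% to 29%, according to whether the shared procedures produce 1.7, 0.85 or 0.5 mm. Under equal membranes the A versus B test stays near 5%. The range depends on two quantities that the article does not give, the shared part of the change and the correlation, and it applies to PPD only. The conclusion that the paired tests cannot isolate a membrane effect depends on neither. It follows from the shared surgery and putty and from the absence of an arm without a membrane.

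**What to change.** 1. In Statistical Analysis, replace the paired tests with the mean within-arm change and its 95% confidence interval, labelled descriptive, with no significance label.
2. In the same section, state that conclusions on effectiveness rest on the A minus B difference, and name bone fill, the primary outcome, alongside PPD reduction and CAL gain.
3. State that the trial cannot show that either membrane adds to flap surgery plus putty.
4. In the abstract's Results, word the anticipated benefit of AmnioGuard as relative to A-PRF plus NovaBone Putty, as the closing Conclusions section already does.

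The cost is text only: no extra patients, visits or measurements. The article reports 4 participants enrolled and analysis not complete at submission, so the change can be made before results are known. The downside is that the per-arm P values are given up.

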**Methods:**

A total of 24 patients will be selected and divided into 2 groups: group A (n=12, 50%) and group B (n=12, 50%). Group A will receive treatment with NovaBone Putty and AmnioGuard, whereas group B will receive treatment with autologous A-PRF and NovaBone Putty. Plaque index, clinical attachment level, probing pocket depth, complete mouth bleeding score, and intraoral periapical radiographs will be statistically analyzed. Clinical and radiographic features will be evaluated before surgery and 6 months following the procedure.

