## Results

Ethical approval was obtained from the Institutional Ethics Committee of Datta Meghe Institute of Higher Education & Research on February 7, 2025. Recruitment began on September 16, 2025, and is ongoing. As of manuscript submission, 4 participants have been enrolled. Data collection is ongoing, and data analysis has not yet been completed. Results are expected to be published in 2027.

All the clinical measurements will be recorded at baseline and 6 months. Plaque index, which indicates the degree of full-mouth supragingival plaque accumulation, will be used to assess the patient’s dental hygiene status and will be measured at the 1-month follow-up. Although a substantial difference between the groups is not anticipated, AmnioGuard and NovaBone Putty should show better results and improvement in clinical outcomes such as CAL gain and PPD reduction.

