### Limitations

The follow-up duration is relatively short (3‐6 months), which may not fully capture the long-term stability and success of the regenerative treatment. Future studies with extended follow-up periods are needed to evaluate the durability of the clinical and radiographic improvements observed. The study will be conducted at a single institution (Sharad Pawar Dental College), which may limit the generalizability of the findings to broader populations with diverse demographic characteristics and clinical backgrounds. Multicenter studies would help improve external validity. The participants in this study may present with varying degrees of periodontal defect severity, which could introduce heterogeneity in treatment responses and influence the observed outcomes. The success of periodontal regenerative therapy is strongly influenced by patient compliance with postoperative oral hygiene instructions and maintenance care. Variability in individual patient cooperation could impact healing and regenerative results.

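### The between-arm t tests, including those on change scores, ignore the planned baseline values; ANCOVA would be valid, usually more precise and almost free, and should also cover bone fill

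*Protocol article*

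**What the plan says.** The Statistical Analysis section names two sets of tests. The first is general: two-tailed t tests, both unpaired and paired, "will be used to evaluate data at baseline and 6 months for each group". The second is the comparison of group A with group B on plaque index, full-mouth bleeding score, "PPD reduction, and CAL gain using an unpaired *t* test". PPD reduction and CAL gain are changes from baseline. No covariate appears in either sentence.

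Baseline data are planned for both kinds of outcome. Results states: "All the clinical measurements will be recorded at baseline and 6 months". The Abstract (Methods) states: "Clinical and radiographic features will be evaluated before surgery and 6 months following the procedure".

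Evaluation Outcomes states: "The primary outcome of this study is radiographic bone fill at 6 months after surgery". Bone fill is not in the list of between-arm tests. The Abstract says only that the radiographs will be analyzed statistically.

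Limitations expects participants to present with "varying degrees of periodontal defect severity, which could introduce heterogeneity in treatment responses and influence the observed outcomes".

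**The concern.** The objective is comparative and the trial is small. An unadjusted change score subtracts the whole baseline value. That over-corrects whenever the regression slope of the 6-month value on baseline is below 1, and it adds baseline noise to the contrast. An unadjusted 6-month comparison makes no correction at all. In both cases a chance difference in baseline severity between two groups of 12 passes into the estimate. ANCOVA estimates the slope from the data and largely removes that component.

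The stake is precision rather than bias over repeated trials. The article does not anticipate a substantial difference between the arms, so a wide interval is the likeliest way for this trial to end without an answer. The primary outcome is affected too, because its between-arm test is not named.

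**Working it through.** **Inputs from Sample Size Estimations.** PPD SD before 1.17 mm, SD after 1.10 mm, 12 per arm, and a test "corresponding to a 2-sided significance level (α) of .05, which equals a 95% confidence level".

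**Assumptions, not in the article.** The baseline to 6-month correlation ρ, shown at 0.3, 0.5 and 0.7. A between-arm difference of 1.0 mm, purely illustrative. The article's 1.7 mm is a before-after change in one arm, and it gives no numeric between-arm difference.

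**1. The plan's own figure.** (1.96 + 1.64)² × (1.17² + 1.10²) / 1.7² = 12.96 × 2.5789 / 2.89 = 11.56, which rounds up to 12 per group. It reproduces.

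**2. Variance per participant under each analysis.**
- 6-month value: 1.10² = 1.21.
- Change score: 1.17² + 1.10² − 2ρ(1.17)(1.10) = 2.5789 − 2.574ρ.
- ANCOVA: 1.21(1 − ρ²), multiplied by 1 + 1/(24 − 4) = 1.05 for chance baseline imbalance.

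**3. Precision and power.** The SE of the difference is √(2 × variance / 12). The t tests have 22 df (critical value 2.074) and ANCOVA has 21 (2.080). Power is for 1.0 mm, from the noncentral t.

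| ρ | Change-score variance | ANCOVA variance (× 1.05) | Ratio | 95% CI half-width: 6-month / change / ANCOVA (mm) | Power: 6-month / change / ANCOVA |
|---|---|---|---|---|---|
| 0.3 | 1.807 | 1.156 | 0.64 | 0.93 / 1.14 / 0.91 | 57% / 41% / 59% |
| 0.5 | 1.292 | 0.953 | 0.74 | 0.93 / 0.96 / 0.83 | 57% / 54% / 67% |
| 0.7 | 0.777 | 0.648 | 0.83 | 0.93 / 0.75 / 0.68 | 57% / 76% / 82% |

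The ANCOVA power figures are good to about one percentage point; this formula alone gives 58.4%, 66.8% and 82.7%. Without the factor 1.05 the variance ratios would be 0.61/0.70/0.79, which overstates the gain.

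**4. Where the gain stops.** Against the 6-month test, ANCOVA needs 1.05(1 − ρ²) < 1, so ρ above √(1 − 1/1.05) = 0.22, or about 0.23 on CI width once the lost degree of freedom is counted. Against the change score, ANCOVA is still ahead at ρ = 0.9: 1.05 × 1.21 × 0.19 / (2.5789 − 2.3166) = 0.241 / 0.262 = 0.92.

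**5. Chance imbalance.** The SE of the baseline difference is 1.17 × √(2/12) = 0.48 mm, so a gap above 0.5 mm in either direction occurs in about 30% of trials (0.5/0.478 = 1.05 SE). At ρ = 0.5 the slope is 0.5 × 1.10/1.17 = 0.47. A 0.5 mm gap then shifts the change-score estimate by 0.5 × (1 − 0.47) = 0.26 mm and the 6-month estimate by 0.5 × 0.47 = 0.24 mm.

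**6. Validity.** With no true difference, simulated trials of 12 per arm rejected in about 5% of cases for all three analyses.

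**7. Within-arm tests.** For a 1.7 mm change in 12 participants, paired-test power is 97.8%, 99.7% and above 99.9% at ρ = 0.3, 0.5 and 0.7. A significant result is close to certain in any arm that improves this much, so it says little about which arm is better.

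**The case against.** The strongest reply is that unadjusted t tests between randomized arms are legitimate, so this is a preference between two valid methods. The validity part stands: nothing here inflates type I error. A preference that costs one degree of freedom is still worth acting on at this sample size. Covariate adjustment is often left to an analysis plan that is not shown, but here the article states the method, so the choice is open to comment.

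The size of the gain is also conditional, and that stands. Neither ρ nor the 1.0 mm comes from the article. At ρ = 0.3 the gain over a 6-month test is about 2 points, and at ρ = 0.7 the gain over the change score is about 6. Every figure is for PPD, a secondary outcome; the article gives no SD or correlation for bone fill.

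Four stronger readings are tempting, and the text does not support them:
- That the plan lacks a between-arm comparison. The last sentence of Statistical Analysis makes one; ANCOVA refines it.
- That the arms will be judged by setting one within-arm P value against the other. No such comparison is planned; the paired tests stand beside a between-arm test.
- That baseline differences will be tested for significance. The sentence is loose. It can equally mean paired tests over time and unpaired tests between arms.
- That Limitations admits to uncorrected baseline imbalance. It speaks of heterogeneous response to treatment, which makes severity a sensible covariate but says no more.

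**Conclusion.** The point holds as one of precision and robustness. The stated between-arm tests are valid but leave planned baseline information unused. For PPD, with the article's SDs, ANCOVA has about 0.64 to 0.83 of the variance of the change-score test over ρ of 0.3 to 0.7. For an assumed 1.0 mm difference that is worth roughly 6 to 18 points of power. Compared with a 6-month-only test the gain runs from about 2 to 25 points over the same range and vanishes near ρ = 0.2, where the two are level. For bone fill no size can be given. The firmer criticism there is that the primary outcome is not named in the list of between-arm tests.

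**What to change.** In Statistical Analysis, replace the unadjusted between-arm tests as follows:
- PPD and CAL: ANCOVA of the 6-month value on arm and the baseline value of the same measure.
- Radiographic bone fill: name it as the primary between-arm comparison, by ANCOVA on arm and baseline radiographic defect depth.
- Report each adjusted difference with its 95% CI.
- Keep the within-arm paired tests as description only.
- Reword the general sentence so that it is clear which test applies to which data. If it intends significance tests of baseline differences between the arms, drop them: randomization already makes that null hypothesis true.

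The cost is one degree of freedom and a change of wording. No new measurements are needed. Four participants had been enrolled at submission and the analysis was not complete, so the change can still be prespecified.

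### Radiographic bone fill is the declared primary outcome, but the sentence naming the between-group tests omits it, and the stated 95% power comes from a within-treatment change in PPD

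*Protocol article*

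**What the plan says.** **Outcome hierarchy (Evaluation Outcomes).** "The primary outcome of this study is radiographic bone fill at 6 months after surgery". The same section continues: "The secondary outcomes are PPD reduction, plaque index, papillary bleeding index, and CAL gain".

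**Analysis (Statistical Analysis).** A general sentence gives the tests without naming an outcome: "Unpaired and paired 2-tailed *t* tests will be used to evaluate data at baseline and 6 months for each group". The section's last sentence names outcomes for the unpaired t test between groups: "Group A and group B will be compared based on clinical outcomes of plaque index, full-mouth bleeding score, PPD reduction, and CAL gain".

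**Sample size (Sample Size Estimations).** The inputs are PPD values for one treatment combination. The first is "Mean PPD for AmnioGuard and NovaBone Putty (μ₁) before: 8.6 (SD 1.17" mm; the second is the same combination afterwards, 6.9 mm (SD 1.10). With two-sided alpha .05 and 95% power, the section arrives at 12 per group and concludes: "The minimum total sample size required is 24".

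**Other mentions of the radiographs.** The abstract's Methods paragraph says that "intraoral periapical radiographs will be statistically analyzed". The Objectives section includes radiographic bone fill in the comparison of the two combinations.

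**The concern.** The outcome called primary, the outcomes named for the group comparison and the outcome used for sizing should agree. Here the first is bone fill, the second are four clinical measures, and the third is PPD.

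Two things are at stake. First, the article's Conclusions section anticipates that one combination may do better at regenerating bone, but no sentence fixes the bone-fill comparison on which that claim would rest. If it is not fixed in advance, the role of bone fill relative to the clinical measures is left open once results are known. Second, a reader will take 95% power to describe the comparison of AmnioGuard with A-PRF. The calculation supports no such statement, for bone fill or for PPD.

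**Working it through.** **1. Outcomes side by side.**

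| Outcome | Rank in Evaluation Outcomes | Named for the group A versus B t test | Used for sizing |
|---|---|---|---|
| Radiographic bone fill, 6 months | Primary | No | No |
| PPD reduction | Secondary | Yes | PPD level before and after, one treatment |
| CAL gain | Secondary | Yes | No |
| Plaque index | Secondary | Yes | No |
| Papillary bleeding index | Secondary | No | No |
| Full-mouth bleeding score | Not listed | Yes | No |

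The last two rows show a second, smaller mismatch: the two sections give the bleeding outcome different names.

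**2. Reproducing the plan's figure.** Inputs from Sample Size Estimations: Z values 1.96 and 1.64; SDs 1.17 and 1.10; means 8.6 and 6.9; ratio r = 1.

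n = (1.96 + 1.64)² × (1.17² + 1.10²) / (8.6 − 6.9)²
= 12.96 × 2.5789 / 2.89
= 11.56, rounded up to 12 per group.

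The arithmetic is right. It also shows that the sizing rests on PPD alone.

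**3. What the 1.7 mm is.** Both means belong to AmnioGuard with NovaBone Putty, one before and one after treatment. Their difference, 8.6 − 6.9 = 1.7 mm, is a change within one treatment. No value for A-PRF with NovaBone Putty enters. The formula is the one for two independent groups, so it treats this change as if it were the difference between the two arms. As a standardised difference it is 1.7 / √(2.5789/2) = 1.7 / 1.136 = 1.50 SD. The Results section says that no substantial difference between the groups is anticipated.

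**4. What 12 per group can detect.** For an unpaired t test with 22 degrees of freedom and two-sided alpha .05, the critical value is 2.074 and the noncentrality parameter is d × √(12/2), where d is the between-group difference in SD units. Solving for d:

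- 80% power: d = 1.20
- 95% power: d = 1.54

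Power at assumed values of d (illustration only, since the article gives neither an expected difference nor an SD for bone fill):

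| Assumed d | Power with 12 per group |
|---|---|
| 0.5 | 22% |
| 0.8 | 47% |
| 1.0 | 65% |
| 1.2 | 80% |
| 1.5 | 94% |

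These figures hold for any continuous outcome compared between two groups of 12, bone fill included.

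**The case against.** The strongest reply is that the bone-fill comparison is poorly specified rather than absent. The general t-test sentence excludes no outcome, and an unpaired test is naturally a between-group test. The abstract says the radiographs will be analysed, and the Objectives section puts bone fill in the comparison. The sentence listing four outcomes is limited to clinical ones, so a radiographic outcome could fall outside its scope. This much stands. A reader might infer that the plan contains no comparison of its primary outcome at all; the documents do not support that. What remains is that none of these sentences names a between-group bone-fill test or makes it the primary analysis.

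Three further inferences are tempting and also go too far.

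- **That the four listed tests have equal standing, so that any one could carry the conclusion.** Evaluation Outcomes already ranks bone fill above the others, and no sentence says that the conclusion may come from whichever test is significant. A familywise error of about 19% (1 − 0.95⁴ = 0.185) would need that reading and independent outcomes as well, so it is not a measure of this defect.
- **That success is defined by CAL and PPD.** The Results section says the AmnioGuard combination "should show better results and improvement in clinical outcomes such as CAL gain and PPD reduction". That is an expectation, not a success criterion, and the Conclusions section is worded on bone regeneration.
- **That the trial is shown to be underpowered for bone fill.** Without a bone-fill SD or expected difference, the detectable differences above do not show this. They show only that the stated 95% has no basis for the group comparison.

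Nor is this detail that an article may leave to a fuller document. The article does name its between-group outcomes and its sizing variable, and neither matches its own primary outcome.

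**Conclusion.** The point holds in this form: the primary outcome is not named in the between-group analysis, and the sample size rests on a within-treatment change in a secondary outcome. The figure of 12 per group is arithmetically correct, but the 95% power attached to it applies neither to bone fill nor to a between-group difference in PPD.

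What can be said of 12 per group is that it detects about 1.20 SD at 80% power and 1.54 SD at 95% power. This assumes 12 analysed participants per arm, one value per participant, approximate normality and equal variances. Whether differences of that size in bone fill are plausible cannot be judged from the article.

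This should be corrected before analysis. The article reports 4 of the planned 24 participants enrolled at submission and analysis not yet completed, so the primary comparison can still be fixed before results are known.

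**What to change.** **Statistical Analysis.** Name the difference between group A and group B in 6-month radiographic bone fill as the primary analysis (unpaired t test, two-sided alpha .05, with 95% CI), and say that the comparative conclusion rests on it. Describe the tests of the outcomes that Evaluation Outcomes calls secondary as supportive. Reconcile full-mouth bleeding score with papillary bleeding index, so that both sections name the same measure.

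**Sample Size Estimations.** Withdraw the 95% power claim for the group comparison. State that the calculation used a before/after change in PPD within one treatment. State that 12 per group detects a between-group difference of about 1.20 SD at 80% power, or 1.54 SD at 95% power, on any continuous outcome including bone fill, and that no bone-fill SD was available. Merely relabelling the existing calculation as one for a secondary outcome would not be enough, because it would still appear to support the between-group PPD test.

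**Cost.** The changes are to wording. The radiographs are already planned, and no extra patients or procedures are needed. The price is a less favourable statement of power.
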